#### Strategies to improve adherence to interventions {11c}

Participants will be reminded regularly by the research nurse of the online sessions. A complete timetable of online sessions will be provided for each participant at the inclusion. Phone messages and email reminders will be sent 24 h and 1 h before each online session. Similar procedures will be implemented regarding the online assessment battery comprising a set of validated self-report measures at each time point. In case of absence, the patient will receive a phone call from the research nurse within 24 h later.

#### Relevant concomitant care permitted or prohibited during the trial {11d}

Patients enrolled in the study are prohibited from receiving any psychological or formal psychiatric treatment during the trial.

#### Provisions for post-trial care {30}

Following ethical requirements, participants assigned to the control condition (i.e. TAU) will be given the opportunity to receive the newly developed intervention afterwards. Those undergoing the experimental condition (MITIG.RA) will be referred, in case they wish so, to further individual psychological support.

### Outcomes {12}

#### Primary outcome

The following is the primary outcome:Fatigue: Fatigue levels will be assessed by the 0–10 numerical rating scale assessing fatigue as part of the RAID [54], described below. Changes at the 3-month follow-up after the second booster session, i.e. 32nd week will be considered.

#### Secondary outcomes

The following is the secondary outcomes:Satisfaction with disease status—PESS: The Patient Experienced Symptom State (PESS) [56] evaluates the patients’ degree of satisfaction with their RA status during the last week, through a single item rated on a 5-level Likert scale response (‘very bad’, ‘bad’, ‘acceptable’, ‘good’, and ‘very good’).Perceived impact of disease—RAID and RAID.7: The RAID is a 7-item patient-derived measure designed to evaluate the patients’ perceived impact of RA upon important health-related domains, namely pain, functional disability, fatigue, sleep, physical well-being, emotional well-being, and coping. The items are rated using 11-point numeric rating scales. Domains can be combined into a single score (RAID) [55, 62] or used separately (RAID.7) [54]. Higher scores indicate a greater impact of disease.Anxiety and depression—HADS: Levels of emotional distress will be measured through the Hospital Anxiety and Depression Scale [63, 64]. This scale comprises 14 items, rated on a 4-point Likert scale, aimed at screening for the presence and severity of anxiety and depressive symptoms in the last 7 days. Higher values are indicative of more severe levels of symptoms, with a cut-off score of 11 being indicative of a clinically significant mood/anxiety disorder.Self-compassion—SCS-sv: Self-compassion will be assessed by the Self-Compassion Scale [65, 66]. This 12-item measure is a shorter form of the original scale developed by Neff [67] and aims to assess the type of relationship one establishes with oneself in the face of setbacks or difficult times. Items are rated on a 5-point Likert scale, with greater values indicating greater levels of self-compassion. While several factorial solutions have been proposed, in this study, we will use a two-factor structure, comprising the self-compassionate attitude subscale and the self-critical attitude subscale.Psychological flexibility—CompACT: Psychological flexibility, a key construct in ACT, will be assessed through the Comprehensive Assessment of Acceptance and Commitment Therapy (CompACT) [68]. This is a 23-item self-report measure rated using a 7-point response scale from 0 (‘strongly disagree’) to 7 (‘strongly agree’). The scale comprises 3 factors, namely openness to experience (e.g. ‘I can take thoughts and feelings as they come, without attempting to control or avoid them’), behavioural awareness (e.g. ‘I do jobs or tasks automatically, without being aware of what I am doing’), and valued action (e.g. ‘I can identify the things that really matter to me in life and pursue them’). Scores range from 0 to 60 (openness to experience subscale), 0 to 30 (behavioural awareness subscale), 0 to 48 (valued action subscale), and 0 to 138 (total score) and are computed by summing all respective items. Higher scores indicate greater psychological flexibility.Patient global assessment of disease activity—PGA: In our study, the PGA will not be used as an outcome measure but as a tool used to define eligibility. PGA is one of the most widely used patient-reported outcomes in RA and is found in several scores, such as the 28-Joint Disease Activity Score (DAS-28). The PGA is a holistic assessment of disease that goes beyond the objective measures of inflammation (acute phase reactants) and/or structural damage (radiographic) [66, 69]Clique ou toque aqui para introduzir texto.. Higher scores represent a higher level of disease activity or a worse global health, since the proposed definition of ‘low global assessment’ is ≤ 2.0 on a 0 to 10 scale [70].Safety of the intervention: Safety-related outcomes will be evaluated through participants’ reporting of adverse events and will include information regarding the nature/type of adverse event, duration and frequency of the event, and degree of association with the intervention (‘no’, ‘probably’, ‘possibly’, ‘yes’).Feasibility and acceptability: Feasibility will not be formally assessed in this study as they seem well-established in the literature regarding similar interventions in similar contexts [51, 61]. However, all aspects related to these dimensions will be proactively monitored and registered, namely through rates of attendance and drop-out and the respective underlying reasons.

#### Participant timeline {13}

See Fig. 1 for the SPIRIT figure with the participant timeline.

**Fig. 1 Fig1:**
[figure not shown]
Schedule of enrolment, intervention, and assessments. Legend: *only for the experimental (active) condition. Booster sessions at 1- and 3-month follow-ups are considered as part of the intervention: T0 = baseline; T1 =post-intervention; T2 = before 1st booster session; T3 = before 2nd booster session; T4 = 12-week follow-up; T5 = 24-week follow-up. MITIG.RA, Compassion and Mindfulness Intervention for Rheumatoid Arthritis; TAU, treatment-as-usual; RAID, Rheumatoid Arthritis Impact of Disease; DAS28CRP3v, Disease Activity Score using 28 joints and C reactive protein and three variables; PGA, Patient Global Assessment of disease activity; PESS, Patient Experienced Symptom State; HADS, Hospital Anxiety Depression Scale; SCS-sv, Self-Compassion Scale; CompACT, Comprehensive Assessment of Acceptance and Commitment Therapy

#### Sample size {14}

The primary outcome of the study will be the difference in fatigue scores between the two intervention groups at week 32, controlling for baseline values. Based on the minimum clinical improvement established for RAID score and on our previous study assessing the responsiveness of RAID.7i, we expect a minimum difference in fatigue scores between the two groups of at least 3 points [54, 71, 72].

A sample size of 91 was indicated by G*Power for analysis of covariance (ANCOVA) [*α* = 0.05, 90% statistical power, effect size of 0.50]. Assuming a 30% attrition rate and rounding up for convenience, we plan to recruit a total of 120 participants (60 participants per arm).

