### Trial design {8}

The MITIG.RA is a two-arm parallel superiority randomized controlled trial. Participants will be randomized (1:1) into one of two conditions: the experimental condition (MITIG.RA programme plus TAU) and the control condition (TAU only). The first version of the protocol was registered in ClinicalTrials.gov (NCT05389189) in May 2022, before the enrolment of patients. This protocol was written in accordance with the Standard Protocol Items: Recommendations for Interventional Trials (SPIRIT) guidelines. The Consolidated Standards of Reporting Trials (CONSORT) guidelines will be followed when reporting the results of the study.

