## Discussion

By combining components of contextual CBT interventions, we have designed a new psychosocial intervention aiming at the management of fatigue in RA patients. Fatigue is recognized as a frequent and important manifestation of RA which is typically very difficult to manage in practice. Although fatigue constitutes our primary endpoint, other relevant related domains, including the impact of disease, depression, and anxiety, will also be assessed and addressed and, hopefully, improved.

Although classical CBT interventions have been found to be useful in the past, effect sizes are relatively small and considered unsatisfactory [26, 27, 61, 74, 75].

The interventions’ core comprises practices of mindfulness, acceptance, and compassion-based interventions, designed to promote relevant changes in the bidirectional interplay between physical and psychological experiences endured by patients with RA. The key strength of the intervention is found in the emerging validity of CCBT interventions in diseases where body and mind are both potentially and interactively affected [37, 76–78]. A group format is not only cost-effective in nature [79] but also recognized as a powerful element in interventions focused on coping, chronic pain, mood, and disability [80]. At the same time, an online delivery method may be particularly suitable for people who due to accessibility, mobility, financial, or chronic-related disability issues are often unable to enrol at in-person modalities [35].

This study features a number of strengths. The study is focused on the management of fatigue in RA patients, which is challenging in clinical practice, demanding more research on effective interventions. The study is based on a solid methodology, applies a randomized controlled trial, and involves an experienced multidisciplinary team.

The repeated assessment of outcome measures at different moments in time will allow us to evaluate the efficacy and usefulness of the intervention and the booster sessions and the persistence of potential therapeutic gains up to 6 months after the end of the intervention.

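### The stated inputs do not give N = 91 for a two-arm ANCOVA: they give 45 if 0.50 is Cohen's f and 171 if it is Cohen's d with no covariate gain

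*Protocol article*

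**What the plan says.** Under Sample size {14} the protocol article states: "A sample size of 91 was indicated by G*Power for analysis of covariance (ANCOVA", with the bracketed inputs alpha 0.05, "90% statistical power, effect size of 0.50". It does not say whether 0.50 is Cohen's f or Cohen's d.

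The same section gives the target on the raw scale: "we expect a minimum difference in fatigue scores between the two groups of at least 3 points". It then allows for 30% attrition and plans 120 participants, 60 per arm.

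The test is fixed elsewhere. Under Trial design {8}: "Participants will be randomized (1:1) into one of two conditions". Statistical methods {20a} specifies ANCOVA of fatigue at week 32 with the baseline value controlled. Under Primary outcome the measure is the 0–10 "numerical rating scale assessing fatigue as part of the RAID".

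**The concern.** A sample size should follow from the inputs printed beside it. Here one effect size, one alpha and one power are given for a fully specified test, yet 91 is about twice what one reading of 0.50 requires and about half what the other requires. The choice of metric matters because f = 0.50 is a difference of 1.0 SD between two equal arms, whereas d = 0.50 is half an SD.

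At stake is what the trial can claim about its sensitivity. This paragraph is the only quantitative justification for the primary comparison, and as printed it does not tell a reader whether the trial was sized for a large effect with much to spare or for a moderate effect with perhaps too few patients.

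**Working it through.** **Inputs.** Alpha 0.05, power 0.90, effect size 0.50 and a 3-point difference (Sample size {14}); two arms, 1:1 (Trial design {8}); ANCOVA with baseline as the one covariate (Statistical methods {20a}); 0–10 scale (Primary outcome). Sidedness is not stated; an F test corresponds to two-sided.

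**Formula.** Power = P(F′ > F crit), where F′ is noncentral F with df1 = 1, df2 = N − 2 − 1 and noncentrality λ = f²N. For two equal arms, f = d/2.

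**Step 1: try to reproduce 91.**

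| Reading of 0.50 | f | λ at the N found | Smallest N with power ≥ 0.90 |
|---|---|---|---|
| Cohen's f | 0.50 | 0.25 × 45 = 11.25 | 45 (power 0.899 at 44, 0.906 at 45) |
| Cohen's d, no covariate gain | 0.25 | 0.0625 × 171 = 10.69 | 171 (power 0.8999 at 170, 0.902 at 171) |

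One-sided testing gives 36 and 139. Dropping the covariate or adding a second does not change 45 or 171. None of these is 91. At N = 91 itself, power is 99.7% under f = 0.50 and 65.5% under d = 0.50 without covariate gain.

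**Step 2: what would give 91.** Two routes were found, each needing an input that the article does not contain:
- f = 0.50, 2 groups, 1 covariate, numerator df = 10: power 0.896 at 90 and 0.900 at 91. A two-arm comparison has numerator df = 1.
- d = 0.50 with a baseline-to-week-32 correlation of about 0.69: f = 0.25/√(1 − 0.69²) = 0.345, N = 91. Neighbouring correlations of 0.6 and 0.7 give 110 and 88.

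**Step 3: the 3-point difference.** Implied SD = difference / d.
- 0.50 as f means d = 1.0, so SD = 3/1.0 = 3. This is possible on a 0–10 scale.
- 0.50 as d: SD = 3/0.50 = 6. The largest SD on a 0–10 scale is 5, with half the values at each end, so this is impossible.

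The only reading that fits the 3 points is therefore f, and f gives 45. The reading that can reach 91 through a correlation is d, and d cannot carry the 3 points.

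**Step 4: power at the number expected to be analysed.** 120 × (1 − 0.30) = 84.

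| Assumption | f | Power at 84 |
|---|---|---|
| 0.50 is f | 0.500 | 99.5% |
| 0.50 is d, correlation 0 (assumed) | 0.250 | 62% |
| 0.50 is d, correlation 0.5 (assumed) | 0.289 | 74% |
| 0.50 is d, correlation 0.6 (assumed) | 0.313 | 81% |
| 0.50 is d, correlation 0.7 (assumed) | 0.350 | 89% |

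**Step 5: what 84 can detect.** With df1 = 1, 90% power needs f = 0.358, a difference of 2 × 0.358 = 0.72 baseline-adjusted SDs. For 80% power, f = 0.31, or 0.62 baseline-adjusted SDs.

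**The case against.** The best defence is that the trial is well powered for the only clinical target it states. For a 3-point difference, power at 84 analysed is above 99.9% with an assumed baseline-adjusted SD of 2 or 2.5, 99.5% with 3, 97% with 3.5 and 92% with 4. An article also condenses the full protocol, so a missing SD or correlation is not in itself an error. Both points stand, and they limit the finding. Neither makes the printed inputs yield the printed 91.

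Several stronger readings are tempting, and the document does not support them:
- A reader might infer that 0.50 and 3 points are irreconcilable. They conflict only if 0.50 is d. As f, they agree at SD 3.
- A reader might infer that the trial is underpowered. The 62% needs 0.50 to be d and the baseline covariate to contribute nothing, although the analysis adjusts for baseline. It is one end of an assumed range.
- A reader might infer that numerator df was entered wrongly. The match at 10 is exact, but nothing in the text records that entry, and a correlation near 0.69 reaches 91 as well.
- A reader might infer that 3 points is an individual-patient threshold misused as a difference between arms, or that it is implausibly large. The first depends on cited sources that are not at hand. For the second, the entry requirement of fatigue of at least 3 is a floor, not an expected mean. The Discussion's remark that "effect sizes are relatively small and considered unsatisfactory" concerns classical CBT, which this programme is meant to improve on. None of these is a contradiction.

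**Conclusion.** The figure is wrong as written. For the planned two-arm, baseline-adjusted ANCOVA, the stated alpha, power and effect size give 45 (f) or 171 (d, no covariate gain), and no reading confined to the stated inputs reconciles 91, 0.50 and 90%. The result rests on numerator df = 1, which the design fixes, and on a two-sided 5% test; the one-sided alternative does not rescue 91.

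The direction of the error cannot be settled from the text. If 0.50 is f, the trial is about twice the size needed for 90% power before attrition (91 against 45). If 0.50 is d, power at 84 runs from 62% to 89% over assumed correlations from 0 to 0.7. The conclusion is that the 90% claim is not supported by its inputs, not that a shortfall has been shown.

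**What to change.** Rewrite the Sample size paragraph:
1. Recalculate with numerator df = 1.
2. State whether 0.50 is Cohen's f or Cohen's d.
3. Give the SD and the baseline-to-week-32 correlation that link the effect size to the 3-point difference, and make the three agree.
4. Keep 120 and state what it delivers: with 84 analysed after 30% attrition, 90% power for about 0.72 and 80% power for about 0.62 baseline-adjusted SDs.

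The cost is one reworded paragraph and no additional patients. According to Trial status, nobody had been enrolled when the article was written, so the correction could be made before any data existed.

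### The target of 120 does not cover 30% attrition from a required 91: it leaves 84 with observed week-32 data and allows for about 24% loss

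*Protocol article*

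**What the plan says.** Section {14} of the protocol article gives the requirement as "A sample size of 91 was indicated by G*Power for analysis of covariance (ANCOVA", with the settings "0.05, 90% statistical power, effect size of 0.50". It then moves to the recruitment target: "Assuming a 30% attrition rate and rounding up for convenience, we plan to recruit a total of 120 participants", which it splits as 60 per arm. Section {8} confirms the layout: "Participants will be randomized (1:1) into one of two conditions".

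Section {20a} makes the primary analysis an ANCOVA of week-32 fatigue adjusted for baseline, by intention to treat where possible. Section {20c} plans multiple imputation for missing data. Section {18a} schedules the self-report battery at baseline and at 8, 12, 20, 32 and 44 weeks.

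The article nowhere says that 91 already includes losses, and it gives no other basis for 120.

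**The concern.** A reader takes the paragraph to mean that 120 randomised, less 30%, leaves the 91 needed for 90% power. It does not, so the requirement, the attrition rate and the target cannot all hold. The likely cause is the common slip of adding the attrition percentage to the required number. What is at stake is the accuracy of the power statement for the primary outcome: at the attrition rate the plan itself assumes, the trial has somewhat less observed information than it says it needs.

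**Working it through.** **Inputs, all from section {14}:** required N = 91, attrition = 30%, target = 120 (60 per arm), alpha = 0.05, power = 90%, effect size = 0.50 with the metric not named.

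**Step 1. Reproduce the target.**
- Multiplying: 91 × (1 + 0.30) = 118.3, so 119 whole participants, rounded up to 120. This agrees with the article, including its remark about rounding up.
- Dividing: 91 / (1 − 0.30) = 130, or 65 per arm. Going from 130 to 120 would be rounding down.

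**Step 2. What 120 delivers.**
- Observed at week 32 with 30% attrition: 120 × 0.70 = 84.
- Shortfall: 91 − 84 = 7, or 7/91 = 8% of the requirement.
- Attrition that 120 covers: 1 − 91/120 = 24.2%.

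**Step 3. Effect on power, taking 91 as the number that gives 90%.** The test is the noncentral F for ANCOVA with two groups and one covariate: noncentrality = f² × N, denominator df = N − 3. The article does not state the numerator df, so two assumptions are shown.

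| Assumption | Power at 91 | Power at 84 |
|---|---|---|
| f = 0.50, numerator df = 10 (inferred; it returns exactly 91) | 90.0% | 86.7% |
| Numerator df = 1, f set to give 90% at 91 (f = 0.344) | 90.0% | 87.5% |

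The loss is about 2.5 to 3.3 percentage points. In the second row, with d = 2f for two equal arms, the effect detectable at 90% power rises from d = 0.69 at 91 to d = 0.72 at 84. These are complete-case figures.

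**Step 4. How far this depends on the 91.** A two-arm comparison has one numerator df. With df = 1 and the stated 0.50:

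| Reading of 0.50 | N needed for 90% | Power at 84 |
|---|---|---|
| Cohen's f = 0.50 | 45 | 99.5% |
| Cohen's d = 0.50 (f = 0.25), no credit for baseline correlation | 171 | 62% |

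Neither reading gives 91.

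**The case against.** Four points can be made for the plan.

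1. *All 120 could be analysed.* Intention to treat with multiple imputation could place every randomised participant in the analysis. A reader might infer from the arithmetic that only 84 will be analysed; the documents do not say so. The 84 is the number with an observed week-32 outcome.

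2. *Imputation can recover information.* A participant who misses week 32 may have fatigue scores from other visits, and an imputation model that uses them recovers part of the loss. It would be too strong to say that imputation restores nothing. Full recovery is not to be expected, though, and someone who leaves before any post-baseline assessment contributes only baseline. The article gives no correlation between visits, so the amount cannot be worked out. It claims no such credit in the sample size either, where attrition is treated as a loss to be offset.

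3. *The power figure at 84 rests on an inference.* This stands. Numerator df = 10 is not stated; it was found by searching for a setting that returns 91, and it does not suit two arms. The 86.7% is therefore conditional. The 87.5% from a one-df test calibrated to the plan's own 90% at 91 shows that the size of the loss hardly depends on that inference, provided 91 is accepted.

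4. *The loss is small beside the doubt about 91.* This also stands, and it limits the severity. It does not remove the inconsistency, because a corrected base number inflated in the same way would again fall short.

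**Conclusion.** The point holds as a minor correction of a stated figure. The counts (130, 84, 24.2%) need no assumption beyond the article's own numbers. The drop from 90% to about 87% assumes that 91 gives 90% power, that attrition reaches 30%, and that only observed week-32 outcomes count; imputation would soften it to an unknown degree.

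A reader might go further and conclude that the trial is materially underpowered because of this step. The documents do not support that. A loss of about three points changes no design feature or analysis. Whether power is adequate turns on what 0.50 means and which numerator df applies: at 84 observed, power runs from about 62% to 99.5% across the two readings shown, and the attrition step settles neither.

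**What to change.** 1. Recheck the base number first. Name the effect-size metric, use numerator df = 1 for the two-arm ANCOVA, and state any baseline correlation that is assumed.
2. Keep 120 and restate the attrition sentence in one of two ways. If 91 is retained, say that 120 allows for about 24% attrition. Otherwise say that 30% attrition leaves 84 with observed week-32 data, and give the power or detectable effect recomputed at 84 on the corrected calculation.
3. If the sponsor wants to keep both 91 and 30%, the consistent target is 130 (65 per arm). If the base number changes, divide the new one by 0.70.

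Keeping 120 costs one sentence and a slightly less favourable allowance or power figure; moving to 130 costs 10 more participants. The Trial status section reports that no patient had been enrolled, so on that status the text can be corrected before any data exist.

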#### Recruitment {15}

Patients will be recruited from the rheumatology outpatient clinic. Currently, more than 1300 RA patients have regular follow-ups in our department, 700 being below the age of 65 years, and around 40% are in PGA-near-remission. All rheumatologists from our department will be informed about the study, and a kind reminder will be sent every week. Additionally, our research nurse will verify the patients’ registry to identify potential candidates to participate in the study.

